### Study population

#### Proposed sample size

In selecting a sample size we have based our estimates on six factors: 1) the size of effect observed in our previous research; 2) the fact that school will be the unit of randomisation and adolescents will be clustered within schools; 3) a likely dropout rate based on our previous research; 4) an estimate of the intra-class correlation coefficient (ICC); 5) choice of significance level at 5% and sought power of at least 90%; and 6) a correction for imbalances in recruitment or drop-out rates across schools. Based on these values we have estimated the power of our study to detect differences between intervention and control arms of the RCT using our proposed sample sizes. In relation to effect size, our explanatory trial [8] indicated that the intervention reduced objectively assessed smoking rates from around 14% to around 4% (in unadjusted data) in 15–16 year olds. In the analysis controlling for other predictors of smoking and the multilevel nature of the data (children clustered within classes, classes clustered within schools) this equated to a large effect size with an odds ratio of 0.15 (95%CI: 0.03–0.80). We have conservatively powered the present study using a value at the upper end of this range, i.e., to detect a difference of 5% between the intervention (9% rate of smoking initiation) and control (14% rate of smoking initiation) arms at the end of the study (i.e., equivalent to an odds ratio of 0.61). In relation to dropout rates we have estimated that 85% of those who begin the study will be available to follow-up at 48 months [8]. For ICC we have estimated a value of 0.01 based on previous research [8]. In relation to significance level we have used an alpha of 0.05 using a two-sided test in order to be open to testing the possibility that the intervention actually increased smoking initiation rates. In relation to a correction factor to allow for imbalances in recruitment or dropout we estimate this will not reduce our statistical power by more than 1%.

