Using these assumptions we have estimated that we require a total of 36 schools with 18 randomly allocated to the intervention arm and 18 to the control arm of the RCT. Within each school, we estimate that we need to approach at least 120 adolescents at baseline (approximately 4 classes per school). Based on an 85% recruitment rate (due to refusal to participate and non-attendance on testing days) the overall number of adolescents available for analysis will be: 0.85 * 18 * 120 = 1836 per group. The effective number of adolescents per group will be reduced further due to a design effect (i.e., adolescents clustered by school): Design effect = 1 + (m – 1)*ICC, where m is the number of participants per cluster. This yields a design effect of 2.01 and reduces the effective sample size per group to 913 (1836/2.01). This effective sample size yields a statistical power of 90.65% to detect a 5% difference in smoking initiation between the intervention (9% initiation) and control (14% initiation) arms using a two-sided test with an alpha of 0.05. Adding our correction factor for potential imbalances in recruitment would still provide a power of almost 90%. Therefore our proposed sample size is 4320 adolescents from 36 schools (18 intervention; 18 control), with approximately 120 adolescents being approached per school.

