### Randomisation

The unit of randomisation will be schools and our sample size calculations and analyses takes account of this clustering of the data. We believe randomising by school before the intervention begins is most appropriate in order to reduce the likelihood of contamination between the intervention and control conditions (randomising by individual or classroom risks such contamination). The Trial Statistician (RW) will use a random number generator to randomly allocate schools to the control or intervention arms of the trial. Schools have requested feedback on which condition they are randomised to before giving final agreement to participate and agreeing to send out letters to parents. The trial will therefore deviate from best practice in recruiting children to the trial after rather than before randomisation. We will monitor any consequential effects on participation rates. As we hope to recruit all classes in a school year movement between classes within a school should not be a problem. However, adolescents moving school during the RCT are likely to have missing data. Of those initially participating in the study at age 11–12 years we anticipate a cumulative loss to follow-up at age 15–16 years of 15% (based on our previous research, [8]). We will make efforts to minimize drop out (e.g., attempting to ensure each school is visited on more than one day to collect smoking measures) and any potential biases attributable to drop out will be explored statistically.

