### Ethical considerations

Ethical approval was obtained through the University of Leeds Institute of Psychological Sciences ethics committee (Reference number 12–0155). The University of Leeds will act as trial sponsor. Written informed consent will be obtained from all participating schools. The informed consent of participants’ parents will be sought by letter using an opt-out approach, i.e. parents will have the opportunity to “opt out” of the study if they do not wish their child to take part. Children will receive information sheets about the study and will have the opportunity to not complete the measures.

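### Families are approached after the school knows its arm, and the only safeguard tied to this, monitoring participation rates, cannot show a difference between arms in who joins

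*Protocol article*

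**What the plan says.** The Randomisation section of the protocol article sets the order of events: "Schools have requested feedback on which condition they are randomised to before giving final agreement to participate and agreeing to send out letters to parents". It concedes the consequence: "The trial will therefore deviate from best practice in recruiting children to the trial after rather than before randomisation". The next sentence is the only response attached to it: "We will monitor any consequential effects on participation rates". The statistical exploration of bias promised at the end of that section concerns drop-out, not recruitment.

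Parental consent "will be sought by letter using an opt-out approach" (Ethical considerations), and the letters come from the participating schools (Sampling and recruitment of schools and adolescents). Children may also choose not to complete the measures. Under Discontinuation criteria, children with no baseline data are left out of the intention-to-treat analysis, and multiple imputation covers only those with baseline data.

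The content of the parent letter and pupil information sheet is not given. The article does not say whether they name the arm or differ between arms.

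**The concern.** Randomising schools balances the pupils on their rolls, not the pupils who end up in the analysis. Between the two lie several filters that operate after the school knows its arm: the school's own final agreement, parental opt-out, the child's choice and attendance at baseline. If a school about to run anti-smoking sessions loses different families from a school about to run homework sessions, the arms differ before any treatment is given.

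A participation-rate monitor counts how many join. Two arms can each reach 85% and still lose different people. Because children without baseline data are excluded, imputation cannot bring back those lost at this step. At stake is whether a difference in smoking at 48 months reflects the intervention or the composition of the arms.

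The schools' request explains why the school must know early. It does not require parents and pupils to know before opt-out and baseline are finished.

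**Working it through.** **The plan's own figures (Proposed sample size).** Pupils per arm: 0.85 × 18 × 120 = 1836. Pupils per school: 0.85 × 120 = 102. Design effect: 1 + 101 × 0.01 = 2.01. Effective number per arm: 1836 / 2.01 = 913. The trial is powered "to detect a difference of 5% between the intervention (9% rate of smoking initiation) and control (14% rate of smoking initiation) arms", and "we have used an alpha of 0.05 using a two-sided test". The normal approximation with pooled variance gives 91.8% power. With a continuity correction it gives 90.65%, the stated figure. The sample size calculation is not in dispute.

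**Bias with equal participation rates and no treatment effect.** Let q be the share of pupils lost for reasons related to the arm, and r their smoking risk at 48 months. Take 14% as the overall risk, and assume that all other losses, and all control-arm losses, are unrelated to smoking risk. Then

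risk among intervention participants = (0.14 − q × r) / (1 − q), and bias = 0.14 minus that risk.

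The 15% upper limit for q comes from the plan: "Based on an 85% recruitment rate (due to refusal to participate and non-attendance on testing days". The value r = 28%, twice the overall risk, is an assumption, and so is the direction.

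| q | Participants' risk at r = 28% | Bias (points) | r needed for a 2.5-point bias |
|---|---|---|---|
| 15% | (0.14 − 0.042) / 0.85 = 11.5% | 2.5 | 28.2% |
| 10% | (0.14 − 0.028) / 0.90 = 12.4% | 1.6 | 36.5% |
| 5% | (0.14 − 0.014) / 0.95 = 13.3% | 0.7 | 61.5% |
| 2% | (0.14 − 0.0056) / 0.98 = 13.7% | 0.3 | not possible (maximum 1.8) |

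With q at 15%, r = 21% gives 1.2 points and r = 42% gives 4.9 points.

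**Consequence at the top of the range.** With a 2.5-point bias, no true effect and 913 effective pupils per arm, the chance of a significant result favouring the intervention is 36%, against a nominal 2.5% in that direction.

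**Could baseline data show it?** Suppose the shift runs through a measured marker such as family smoking, with risks of 28% and 7% with and without the marker. Its prevalence is then (0.14 − 0.07) / 0.21 = 33%, and a 2.5-point bias requires a difference between arms of 0.025 / 0.21 = 12 points in the marker. With risks of 42% and 7%, prevalence is 20% and the difference is 0.025 / 0.35 = 7 points. Either would be detected with over 98% power if the marker's ICC were also 0.01. A 0.74-point bias under the first set of risks would move the marker by only 0.0074 / 0.21 = 3.5 points, which is harder to see. Baseline smoking does not help: regular smoking at age 11 is 0.5% (Background), and a proportional shift to 0.5 × 11.5 / 14 = 0.41% would be seen with about 5% power.

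**The case against.** A reader might infer that a bias of half the target effect could pass unseen. The documents do not support that.

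- **Size.** The 2.5-point figure needs the whole 15% to respond to the arm. That 15% combines refusal with absence on testing days, and absence is not a reply to a letter. The same section also gives 85% as the follow-up rate, so the refusing share is nowhere stated separately. Under opt-out consent, inaction means participation, so the arm-related share may be small. At 28% risk, non-participants would include 0.15 × 0.28 / 0.14 = 30% of all future smokers in intervention schools, against 15% in control schools. Any excess risk among absentees common to both arms would largely cancel.
- **Motive.** Child withdrawal says that withdrawn children may still be present for whole-class activities, so opting out may not spare a child the sessions.
- **Unseen.** This is true only of the rate monitor. Attitudes, intentions, self-efficacy, and family and friends' smoking are collected at baseline, and CONSORT reporting for cluster trials is promised. A comparison or adjustment using these data may sit in an analysis plan that is not shown, so its absence here is not a fault.
- **Mechanism.** Nothing says that parents are told the arm. A common letter may already exist.

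All four points stand, and they limit the size and certainty of the bias. They do not make the participation-rate check able to detect a change in composition. Nor do they move the question of what families are told, and when, into an analysis plan: that is a recruitment decision.

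**Conclusion.** The point holds as a design risk left open. Recruitment follows a known allocation, the article concedes this, and the one safeguard it ties to the problem cannot detect what matters. The possible false benefit runs from about 0.3 to 2.5 points for arm-related shares of 2% to 15%, assuming 28% risk among those lost in the intervention arm and typical losses in the control arm. Neither the risk nor the share is in the documents, and the direction could be reversed. At shares of 5% or less, a 2.5-point bias would need an extreme risk (61.5% or more) or could not occur.

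Selection by schools is a separate route. Schools give final agreement after learning their arm, and opt-out consent by parents does nothing to limit that.

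The change is worth making because it is cheap and compatible with what the schools asked for, not because a large bias has been shown.

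**What to change.** 1. Keep early disclosure to the head teacher. Use one identical parent letter and one identical pupil information sheet in both arms, describing both programmes without saying which one the school will run. If such materials already exist, say so in the Randomisation section.
2. Ask schools not to tell families or pupils the arm until opt-out has closed and the baseline carbon monoxide and questionnaire measures are complete. Hold the first session after that.
3. Keep the participation-rate check and add a by-arm comparison of school refusals after allocation, parental opt-outs, absences at baseline, and baseline risk factors. Family and friends' smoking and the smoking cognitions should carry this comparison, because baseline smoking is too rare to show a shift.

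**Cost.** One common set of materials, and possibly a slight delay to the first session. The third step uses data already planned, plus a record of refusals. Parents would decide knowing of two possible programmes rather than the one their school will run. Withholding the arm also depends on the schools' cooperation. Selection by schools that decline after allocation can be reported but not removed while the schools' condition is honoured.

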### Compliance with good practice

• All statistical analyses of primary and secondary outcomes will be carried out under the guidance of the trial statistician (RW).

• HTA guidelines for missing data in RCTs will be followed [20].

• CONSORT guidelines [21,22] for presentation of results from cluster randomised trials will be followed.

• Presentation of results will conform to good practice for presentation of complex interventions [23].

• The flow of clusters and individuals through the trial, from assignment to analysis, will be presented using a flowchart, in accordance with CONSORT guidelines [21,22].

• Intra-class correlation coefficients from the multilevel analyses will be presented following good practice for cluster randomised trials.

### Ethical considerations

Ethical approval was obtained through the University of Leeds Institute of Psychological Sciences ethics committee (Reference number 12–0155). The University of Leeds will act as trial sponsor. Written informed consent will be obtained from all participating schools. The informed consent of participants’ parents will be sought by letter using an opt-out approach, i.e. parents will have the opportunity to “opt out” of the study if they do not wish their child to take part. Children will receive information sheets about the study and will have the opportunity to not complete the measures.

### Data collection methods

The primary outcome measure is smoking initiation based on objective measures at 48 months. A secondary measure will be self-reported smoking. These measures will also be assessed at baseline and at 12, 24, and 36 months post-baseline in order to explore the time periods over which the intervention might be best targeted. These data collection sessions will be completed in classroom time by the researchers and take approximately 30 minutes. Self-reported smoking and measures of cognitions (e.g. attitudes to smoking, intentions to resist smoking, self-efficacy over resisting, family smoking and friends smoking) will be collected via questionnaire completed individually but in a classroom setting. An objective measure of smoking will be completed individually outside a classroom setting. A number of measures of objective smoking are feasible. The two most common measures are breath carbon monoxide measures and saliva cotinine measures. Although saliva cotinine may be more effective in detecting occasional smoking (due to the greater half-life of 16–18 hours versus 4–6 hours in breath carbon monoxide) it also has a number of disadvantages. These include lower acceptability to adolescents, greater cost, and loss of ability to feed back the results to participants immediately. For this reason our objective measure of smoking will be obtained from breath carbon monoxide monitors (Micro+ Smokerlyzer® CO Monitor, Bedfont Scientific Limited, Kent, England). This instrument gives a measure of carbon monoxide in the breath in parts per million (ppm) accurate to within 2% based upon exhaling one breath into the device and has been adapted for use in adolescent samples. Although a number of factors influence carbon monoxide in the breath, recent smoking should significantly elevate levels. Carbon monoxide in the breath can be used as a reliable and valid measure of exposure to cigarette smoking [24], comparable in accuracy to blood carboxyhaemoglobin levels [25]. The Bedfont devices have been demonstrated to give reliable and valid assessments of smoking status [26] and have been employed by various researchers with adolescent samples [8,27]. Our secondary outcome measure, self-reported smoking, will be assessed by standard measures (as used in national surveys and our previous research; [8,28]).

### Intervention

This will be a phase III pragmatic randomised controlled trial conducted in two geographically distinct regions of England (West Yorkshire and Staffordshire) that will provide the information on which to base a decision about roll out of the intervention. The intervention involves asking adolescents to read simple anti-smoking messages and then to form an implementation intention by planning how, where, and when to resist smoking (i.e., refuse the offer of a cigarette). This intervention will be repeated every six months over a period of four years between the ages of 11–12 and 15–16 years (8 occasions; see flow chart of study procedures in Figure 1). The anti-smoking messages focus on simple-to-understand negative consequences of starting smoking and the positive consequences of remaining a never-smoker. The implementation inten-tion intervention is designed to give adolescents simple responses for how to refuse a cigarette and to link them to situations where a cigarette might be offered. Five options will be provided for *how* they could refuse the offer of a cigarette or resist the temptation to smoke (e.g., ‘No thanks, I don’t want to smoke; No thanks, I don’t want the habit; No cancer sticks for me; No thanks, smoking makes you smell bad; No, it’s bad for your health’; see [8]). Participants are required to check the options they plan to use or to write in an additional response. Similarly participants will be required to check *where* they would not smoke (e.g., ‘I will not smoke at school; I will not smoke at home; I will not smoke at a party; I will not smoke with my friends; I will not smoke if offered a cigarette’) and *when* they would not smoke (e.g., ‘I think I can make sure I don’t smoke this term’) and signal agreement with their plan not to smoke by ticking a box. The implementation intention will be presented as a paper and pencil questionnaire that adolescents read and complete in classroom time. Previous evidence has suggested that implementation intentions are more effective among individuals who are motivated to perform the behaviour [17]. Therefore combining the implementation intention with motivational messages is likely to be more effective than using implementation intentions alone. This was the combination used in our previous research [8,12]. The research has broadly followed the MRC framework for developing and evaluating complex interventions to improve health [29,30]. The pre-clinical through phases II testing of this repeated implementation intention intervention have been completed as part of this previous work. In particular, significant work has been completed to develop the intervention and test its feasibility and acceptability in appropriate samples of schoolchildren (see [12]). In the control condition participants will read persuasive messages encouraging them to complete all their home work and they will form an implementation intention in relation to completing all their homework.

The intervention will take place in classroom time and will be led by a teacher using materials provided by the researchers. The materials will include written simple anti-smoking messages (as in our previous research, these will be varied between sessions to reduce boredom) and paper versions of the implementation intentions sheets to be completed. The time required will be no longer than 60 minutes to include an introduction by the teacher, brief classroom discussion, reading of the anti-smoking messages and completion of the paper and pencil implementation intention task. We will negotiate with schools about the least disruptive and most appropriate teaching session in which to implement these sessions (e.g., morning registration). Teachers will be provided with a one-to-two hour training session to introduce them to implementation intentions and anti-smoking messages, and to provide them with advice and written information on how to run the intervention sessions. This training will be conducted by the research team and teachers will be paid for their time. We will negotiate with schools on whether the same or different teachers will run the sessions throughout the trial and it may be necessary to train some additional teachers each year.

### Intervention fidelity

We will assess adherence to the intervention in two ways. First, approximately 10% of intervention sessions will be assessed for adherence to protocol (a mixture of self-report by teachers and observation by researchers). Second, all written implementation intentions sheets will be collected by teachers and passed to research staff and they will be analysed for completeness. In our previous research [8] 73% of adolescents completed implementation intentions sheets on at least 6 occasions (out of a total of 8 occasions). In addition, the number of occasions implementation intentions sheets were completed was unrelated to reduced smoking initiation. In the present trial the impact of number of complete and partially complete implementation intentions sheets on rates of objective and self-reported smoking will be examined statistically. Both sets of data will inform the basis of an intervention fidelity analysis.

### Analyses

#### Analyses of primary and secondary outcome measures

The study uses a two group experimental design with schools of adolescents (all aged 11–12 years at outset) randomly allocated to one of two conditions: a repeated implementation intention condition targeting smoking or a control condition. The primary outcome will be objectively assessed smoking and the secondary outcome measure will be self-reported smoking. A two-level logistic regression will be used to model smoking outcomes at 48 months. Given that drop outs are expected, multiple imputation, based on regression methods, will be undertaken to ‘complete’ the data and ensure efficient analysis. This will be done for all participants for whom baseline data is available (to provide meaningful imputations) and will take into consideration the two-level hierarchical nature of the data. With this approach the results will be unbiased given the general assumption of missing at random (MAR) rather than the more restrictive assumption of missing completely at random (MCAR). Results from the multiple imputations will be combined using Rubin’s rules.

Subgroup analyses will be used to examine any differences between high and low deprived schools, between regions (West Yorkshire versus Staffordshire), and between boys and girls. We will use mediation analyses to explore the extent to which any intervention effects are mediated by changes in the measured cognitions as tested in our previous work (e.g., attitudes to smoking, intentions to resist smoking, self-efficacy to not smoke, etc.; [31-34]).

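### Testing deprivation as high versus low schools probably discards information on whether the effect varies with deprivation, in an analysis resting on about 36 school values

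*Protocol article*

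**What the plan says.** The section Analyses of primary and secondary outcome measures names three factors for subgroup analysis: deprivation, region and sex. For deprivation it says: "Subgroup analyses will be used to examine any differences between high and low deprived schools". The same section plans a two-level logistic regression for smoking at 48 months.

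Deprivation appears nowhere else in the article. No measure, cut-point or stratification is given, and no analysis keeps it graded. A fuller analysis plan may define the measure and the cut, so their absence is not counted as a fault here.

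The section Proposed sample size describes "36 schools with 18 randomly allocated to the intervention arm and 18 to the control arm" and powers the main comparison only. It states no power for any subgroup analysis.

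**The concern.** High and low describe ends of a scale. Comparing two classes treats schools just either side of the cut as different and all schools on one side as alike. When the effect changes gradually with deprivation, that weakens the test.

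The loss matters more here because the deprivation of a school varies only between schools. Thousands of pupils contribute outcomes, but the moderator takes about 36 values. The trial is sized for the main effect, so any interaction test starts with modest power.

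At stake is a secondary question relevant to roll-out, which the article gives as the purpose of the trial: whether the intervention works differently in more deprived schools. A real gradient becomes easier to miss. Defining the cut-point later would not recover the information.

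**Working it through.** **Inputs from Proposed sample size**
- Analysed pupils: "0.85 * 18 * 120 = 1836 per group", which is 102 per school.
- ICC: "For ICC we have estimated a value of 0.01 based on previous research".
- Effective size: "This yields a design effect of 2.01 and reduces the effective sample size per group to 913".
- Target: "to detect a difference of 5% between the intervention (9% rate of smoking initiation) and control (14% rate of smoking initiation) arms".
- Test: "we have used an alpha of 0.05 using a two-sided test".

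**The plan's own figure**
- Design effect = 1 + (102 - 1) × 0.01 = 2.01; 1836 / 2.01 = 913 per arm.
- Power for 14% versus 9% with 913 per arm is 91.8% without continuity correction and 90.65% with it. The article's 90.65% is reproduced.

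**Assumptions not in the article:** a graded school score, a cut at the median, a roughly linear gradient, and the size of that gradient.

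**Information kept by the split.** For a linear interaction this is the squared correlation between the score and its median split.
- Normal score: correlation √(2/π) = 0.798, squared 0.64. This is like using 36 × 0.637 ≈ 23 schools.
- Uniform score: correlation √0.75 = 0.866, squared 0.75. This is like using 27 schools.
- Right-skewed score (lognormal, sigma 0.5): about 0.52, so skewness makes the loss larger.

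**Large-sample power, risk-difference scale**
- SE of the risk difference = √((0.14 × 0.86 + 0.09 × 0.91) / 913) = 0.0149.
- Each half holds half the schools, so the SE of the high-low difference in effects = 2 × 0.0149 = 0.0298.
- Assumed high-low difference of 5 points: z = 0.05 / 0.0298 = 1.68, power about 39%.
- Graded, normal score: z = 1.68 / 0.798 ≈ 2.1, power about 56%.
- Graded, uniform score: z = 1.68 / 0.866 = 1.94, power about 49%.

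**Simulation with 36 schools.** This is the better guide, because a school-level regression with four coefficients leaves only 32 degrees of freedom. The illustrative gradient is 3 points per SD. That is 3 × 2 × 0.798 ≈ 4.8 points between halves for a normal score and 3 × 2 × 0.866 ≈ 5.2 for a uniform one.
- Power is about 31-35% with the split and about 45% with the graded score. With no gradient, both tests reject in about 5-6% of runs.
- Another run of 4000 beta-binomial trials gave 33% versus 48% (normal) and 38% versus 51% (uniform). The level varies with the set-up; the ordering does not.

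**Log-odds scale, 36 schools, simulated power**

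| Interaction per SD | Normal: graded / split | Uniform: graded / split |
|---|---|---|
| 0.3 | 46% / 31% | 47% / 35% |
| 0.4 | 67% / 44% | 70% / 54% |
| 0.5 | 85% / 63% | 86% / 70% |

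The loss is about 12 to 22 points. In the normal approximation, an interaction that the graded test detects with 80% power (0.42 per SD) is detected by the split with about 61% (normal) to 68% (uniform).

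**The case against.** The article gives deprivation half a sentence. High and low may be shorthand in a condensed paper for a question about deprivation in general, with the coding and model left to an analysis plan that is not shown. This stands in part. The measure, the cut and the form of test are not stated, so the point is conditional. But the only form of contrast the article states is two-class, and nothing in it offsets that.

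The size of the loss is also assumed. The article gives no deprivation effect, the gain is smaller with a uniform score than with a normal one, and a true threshold near the cut would cost little or nothing. All of this stands. A difference in false-positive rates does not explain the gain: with no gradient, both tests reject at close to 5%.

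A linear interaction on 36 schools has weaknesses of its own. Outlying schools carry leverage, linearity is assumed, and two subgroup effects are easier to read. This stands and shapes the fix.

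Some stronger readings are tempting. A reader might infer that the plan fixes a median split with nine schools per arm in each half. It states no cut, and the Randomisation section does not mention deprivation. A reader might also take 39% versus 56% as the loss in this trial. Those are large-sample figures for an invented 5-point difference with a normal score. Finally, a reader might see a failure on a main question, but neither of the two listed research questions concerns effect modification.

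**Conclusion.** The point holds as a minor, conditional improvement. If schools are classed from a graded score, the stated contrast is a less efficient test of whether the effect varies with deprivation. With a median cut and a roughly linear gradient, it keeps about 64% to 75% of the information. For a gradient of 3 points per SD, power with 36 schools is about 31-35% against about 45%. The direction is secure under a gradual gradient; the size depends on the shape of the score, the place of the cut and the true form of the gradient.

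The primary analysis, its sample size and its stated power are untouched. Neither version is well powered at that gradient, so a null finding would be inconclusive under both.

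**What to change.** In Analyses of primary and secondary outcome measures, make the test for deprivation an arm-by-deprivation interaction in the planned two-level logistic model, with the school score entered as a continuous (standardised) school-level term. Report the intervention effect at the lower and upper quartiles of the score. Plot school-level results to check linearity and influential schools. Keep the high and low rates as a descriptive display, and describe the analysis as exploratory.

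The cost is one sentence of analysis wording. No new data are needed beyond the score from which schools would be classed. The downsides are the assumption of rough linearity and a slope that is slightly harder to present than two subgroup rates; the quartile effects ease the second.
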